### Assessment

The outcome measures of the RCT are described in the following. Overall, there are three measurement points: during the recruitment of the participants (baseline); 6 weeks after the beginning of the intervention (post intervention); and 6 months after the beginning of the intervention (follow-up). Our time point of primary interest is the post intervention, the closest point to the end of the intervention. The timing for administering each outcome measure is shown in Fig. 2: the speed of improvement concerning the clients’ self-perceived depression level throughout the process is assessed at every session, while all other outcome measures are administered at the three measurement points. In addition to the outcome measures, demographics including gender, age, and socio-economic background will be inquired at the beginning of the intervention. The baseline assessment will also include questions on music background (holding a degree in music, amount and type of music engagement) to provide an overview of sample characteristics. All assessments will be conducted by a medical expert specialised in psychiatric evaluation. The assessor is responsible for contacting and reminding the clients of assessment meetings (pre, post, and follow-up). Our previous trial showed that when treatment is offered for free to the client, the dropout rate remains low. Therefore, we have not developed additional client retention strategies.

**Fig. 2 Fig2:**
[figure not shown]
Schedule of enrolment, interventions, and assessments. GAF Global Assessment of Functioning, HADS-A Hospital Anxiety and Depression Scale—anxiety subscale, IIMT integrative improvisational music therapy, LH listening homework, MADRS Montgomery–Åsberg Depression Rating Scale, RAND-36 quality-of-life survey, RFB resonance frequency breathing

#### Primary outcome

The Montgomery–Åsberg Depression Rating Scale (MADRS) will be used to assess the severity of depressive symptoms, serving as the primary outcome measure of the study. The MADRS consists of 10 questions rated on a scale from 0 to 6, and the rating is based on an interview conducted by a clinician. At the beginning of the study, MADRS will be administered as part of the screening process, thus serving also as the source for determining eligibility for the study.

#### Secondary outcomes

The Hospital Anxiety and Depression Scale (HADS) will be used to assess anxiety. The HADS is a widely used and well-established self-report questionnaire for assessing anxiety and depression in a non-psychiatric adult population. In the present study, only the anxiety subscale will be used (HADS-A). This consists of seven items scored from 0 to 3, with higher scores indicating higher levels of anxiety. The Finnish version of the HADS has been found to be reliable and internally consistent, with a Cronbach’s alpha of 0.83 [52].

Quality of life will be assessed with the RAND-36. The RAND-36 is a health survey with 36 items that focus on eight domains related to quality of life: physical functioning, bodily pain, role limitations due to physical health problems, role limitations due to personal or emotional problems, emotional well-being, social functioning, vitality, and general health perceptions. It is often used to evaluate someone’s quality of life. The RAND-36 has been officially translated into Finnish, and the reliability of the localised version was determined to be adequate, each subscale having a Cronbach’s alpha above 0.80 [53].

The Global Assessment of Functioning (GAF) is a scale used to assess how mental health symptoms are affecting a person’s daily life and general functioning. The GAF is clinician rated and administered through an interview. The scoring ranges from 0 to 100, and the scale is subdivided into 10 sections. The GAF has been officially translated into Finnish by the Social Insurance Institution of Finland (KELA) and is routinely used by health care providers.

A one-item rating of current depression severity will be used as an additional secondary outcome measure for tracking the trajectory of change concerning the client’s self-perceived depression levels. At the beginning of each session, the clinician will ask the participant to describe his or her current level of depression on a scale from 0 = *not at all depressed* to 10 = *extremely depressed*. The clinician stores the numeric answer. This allows us to follow the clients’ self-perceived depression levels throughout the therapy process and assess the speed of recovery.

#### Safety assessments

Based on previous research evidence it can be concluded that a majority of the participants should benefit from the intervention. The treatment model and the measurements associated with it are all non-invasive. Some aspects of the RFB intervention may cause momentary uncomfortable experiences to some of the participants. These will be minimised by appropriate information, by sensitively listening to the experiences of the participants, and by always ensuring that a participant is capable and willing to participate in the activities in question. Possible concomitant care and interventions are not prohibited during the trial.

The intervention (IIMT) may temporarily trigger emotions and experiences perceived as uncomfortable, for instance negative emotions, associations, and feelings related to a certain therapeutic theme, or one’s illness in general. Based on our experience, however, IIMT is not different from typical psychotherapeutic processes where difficult emotions, worries, fear, and feelings of insecurity are temporarily experienced; even temporary worsening of the depression is possible. Due to the relative shortness of the process (12 sessions), the therapists’ training emphasises how to handle the clients’ possible negative experiences within the sessions. For instance, the recommended practice is to try to reduce the emotional intensity of the session towards the end of it so that the client would leave the therapy room as peaceful and calm as possible. These issues are emphasised both in the training of the clinicians before the RCT and in the supervision during the RCT. When ending the therapy session—and, in particular, when ending the whole therapy process—the therapists are instructed to pay particular attention to the client’s overall, emotional well-being.

For the participants, there are two main contexts in which they can give additional feedback regarding the treatment, the first being an electronic questionnaire administered at the end of every session. The questionnaire covers aspects related to the session’s content and impact, as well as the client’s emotional experiences. The second possibility is the post-treatment assessment, where the assessor, in addition to administering the outcome measures, asks the clients for general feedback regarding the treatment and their participation in the trial.

Our previous RCT [2] had a low incidence of adverse events and we expect this rate to remain low in the new RCT. However, in this trial over twice as many clients will receive music therapy and it is possible that the total amount of treatment-related adverse events will be larger than in our previous trial. In addition, the newly introduced elements (RFB and LH) may increase the risk of adverse events. Taking these points into account, we expect to encounter the following categories of adverse events: treatment-model related (some clients may experience IIMT as inappropriate and unpleasant for them, which may cause frustration and/or anxiety); client related (despite the careful initial assessment to ensure meeting of the inclusion criteria, some participants with additional psychiatric disorders may be enrolled; this may lead to unexpected challenges and it is possible that a client’s condition will worsen); and intensity related (bi-weekly sessions and the presence of added treatment components may increase the depth and intensity of psychological/emotional processing, which might cause participants to feel anxious and could lead to a possible worsening of a client’s condition, at least temporarily).

For reporting the adverse events, a form will be created including the description of the incident plus additional information such as date, participant code, time, site, and the name of the staff person (if applicable). A procedure for addressing the report to the right place will be created.

Because of their existing diagnosis, we can assume that the majority of the participants are already being treated inside the mental health care system. For instance, in our previous study, about 70% of the participants took medication for depression before and during the RCT, and were in more or less frequent contact with mental health services. The clinicians will be advised to discuss the possible need for further therapeutic activities with the client. In particular, if the clients have no previous or current contact with the health care system regarding their depression, or if they are unaware of the treatment possibilities, they will be told about the local treatment practices and possibilities. Despite all the precautions, should a client’s condition worsen and no solution be found between the therapist and the client, the therapist is advised to contact the PI. The PI is responsible for starting appropriate actions, for instance contacting an external expert for remedial actions (e.g. the psychiatrist in charge).

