**Fig. 1 Fig1:**
[figure not shown]
RCT flow chart with outcome measures. GAF Global Assessment of Functioning, HADS-A Hospital Anxiety and Depression Scale—anxiety subscale, IIMT integrative improvisational music therapy, LH listening homework, MADRS Montgomery-Åsberg Depression Scale, RAND-36 quality-of-life survey, RFB resonance frequency breathing

An external expert who has no direct contact with the patients will conduct a computerised randomisation procedure. We will employ block randomisation with randomly varying block sizes of 4 and 8. The allocation list will be saved on a password-protected repository with access only by the PI and study coordinator. To ensure allocation concealment, the randomisation will be conducted at another site (Uni Research, Bergen, Norway). As a result, the assessor, the therapists, and the participants will not be able to know the group allocation in advance. Only the outcome assessor will remain blinded to the group allocation throughout the trial. At the time of assessments, participants will be reminded not to reveal their allocation to the assessor. As far as the PI is concerned, he is blinded from the randomisation and the clients’ conditions in general, but because he is also one of the clinicians and participates in supervision he will get to know the condition of some clients. However, the PI is not involved in the client assessments or data entry in any way.

A power calculation was carried out for the primary outcome (depressive symptoms measured by the MADRS), based on the following assumptions.

Prior reviews of music therapy used in the treatment of depression have reported large effect sizes of music therapy compared to standard care. A recent meta-analysis [1], which included nine studies and involves a total of 421 participants, examined the short-term effect of music therapy for depression for primary outcomes. These authors found moderate quality evidence favouring music therapy and treatment as usual (TAU) over TAU alone for both clinician-rated depressive symptoms (SMD – 0.98, 95% CI – 1.69 to − 0.27, three RCTs, one CCT, *n* = 219) and patient-reported depressive symptoms (SMD – 0.85, 95% CI – 1.37 to − 0.34, three RCTs, one CCT, *n* = 142). Regarding IIMT specifically, our previous study found a medium effect size of *d* = 0.65 [2] based on the traditional two-arm design (intervention vs control).

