### Statistical analyses and data management

The statistical analyses will follow an intention-to-treat approach, using all available data regardless of whether the treatment was received as intended. Furthermore, in the event of missing outcome data, participants will remain in the analysis if at least one follow-up time point is available. Sensitivity analysis will be conducted with multiple imputation for missing data and as a per-protocol analysis (treatment as received). All outcome measures (MADRS, HADS, RAND-36, GAF, one-item rating of current depression severity) provide continuous data and will be examined for normality before statistical tests are conducted. The main effects of each intervention (LH vs no LH; RFB vs no RFB) and their interaction (LH × RFB) will be tested for all outcome measures, using a repeated-measures linear mixed-effects model with LH and RFB as factors. This analysis strategy has the advantage of making full use of the factorial design, such that all 68 participants are available for each comparison (as presented in Table 1). All tests will use two-sided 5% significance level, with no adjustments for multiplicity; secondary outcomes will therefore be regarded as exploratory. No interim analyses of effects will be conducted.

Most of the data obtained through scales, questionnaires, and forms will be collected electronically. Should the data be obtained through paper forms, they will be immediately converted to electronic data. Data entries are always made by an assessor who is very familiar with the assessment instruments and can thus easily recognise inaccurate data. The assessor will also double-check the data entries. All of the collected data will be stored on secure servers from the University of Jyväskylä, which includes daily backups. Dedicated password-protected folders will be used for different types of data, with access rights granted only to those researchers allowed to handle the given data.

Personal records of the participants, such as names, contact details, and consent forms, are stored in a locked room, with access only by the PI, assessor, and study coordinator. In all other contexts, client codes will be used instead of personal information.

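### The blinded rater of MADRS and GAF is also assigned to ask clients for feedback on their treatment at the 6-week visit, which puts the trial's only lasting blind at avoidable risk

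*Protocol article*

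**What the plan says.** Randomisation and sample size sets the blinding: "Only the outcome assessor will remain blinded to the group allocation throughout the trial". Participants and therapists know the allocation, and the principal investigator, who also treats and takes part in supervision, will learn it for some clients. The safeguard for the assessor's blind is a reminder: "At the time of assessments, participants will be reminded not to reveal their allocation to the assessor".

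The Assessment section gives one role to all three measurement points (baseline, 6 weeks, 6 months): "All assessments will be conducted by a medical expert specialised in psychiatric evaluation". The 6-week visit is the time point of primary interest. Primary outcome and Secondary outcomes describe MADRS and GAF as clinician ratings from an interview. HADS-A is a self-report questionnaire and RAND-36 a survey.

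Safety assessments then lists two routes for client feedback. One is an electronic questionnaire after every session. The other is the post-treatment visit, where the assessor not only takes the outcome measures but also "asks the clients for general feedback regarding the treatment and their participation in the trial".

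**The concern.** The person who must not learn the arm is told to invite the client to talk about the treatment, at the visit where the primary outcome is rated. All four arms receive the same music therapy. What separates them is whether the client listens to recordings at home and whether each session opens with 10 minutes of tablet-cued breathing. These are concrete, memorable features, and a client asked about the treatment may well mention them.

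The question also serves a safety purpose. The article says that breathing may cause momentary discomfort and that both added components may raise the risk of adverse events. Feedback that does this job would bring up component-specific experiences. A client who keeps to the reminder gives less useful feedback, and one who answers fully reveals a factor level.

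At stake are MADRS and GAF, whose scores depend on the interviewer's judgement. No other blinding in the trial lasts to the end and could stand in for this one.

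**Working it through.** **Passages side by side**

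| Point | Where in the protocol article | Content |
|---|---|---|
| Who stays blinded | Randomisation and sample size | Outcome assessor only |
| Safeguard | Same section | Reminder to participants at assessments |
| Who rates | Assessment | One expert role, all three time points |
| What is rated by interview | Primary outcome; Secondary outcomes | MADRS and GAF |
| Who asks for feedback | Safety assessments | The assessor, at the post-treatment visit |
| Order of feedback and scoring | Not stated | Unknown |

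**What is exposed under each order**

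- Feedback before scoring: the 6-week MADRS and GAF can be rated with the arm known. The 6-month ratings can be too, if the same person makes them.
- Feedback after scoring: the question cannot affect the 6-week ratings. The 6-month MADRS and GAF remain exposed if the same person makes them.

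Neither order protects the 6-month ratings unless the rater changes or the feedback is kept from the rater.

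**The plan's own figure first**

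Inputs from Randomisation and sample size: 34 per level of each factor, two-sided 5%, effect sizes 0.48 and 0.8. With the noncentral t distribution, df = 2 × 34 − 2 = 66, critical value 1.997 and noncentrality d × √(34/2):

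- d = 0.48: noncentrality 1.979, power 49.6% (stated 50%)
- d = 0.8: noncentrality 3.298, power 90.2% (stated 90%)

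The stated power reproduces. This point does not dispute it.

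**Illustration of size**

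The documents give no rate of unblinding and no rating shift, so both are assumed: 25% to 50% of interviews unblinded, and a shift of 1 to 2 MADRS points between factor levels in those interviews.

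Bias = fraction unblinded × shift, so the range runs from 0.25 × 1 = 0.25 points to 0.5 × 2 = 1.0 point.

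With the article's SD of around 7 and no true effect, the rejection rate of the same two-sided t test is:

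| Bias (points) | Bias / 7 (SD) | Rejection rate |
|---|---|---|
| 0 | 0 | 5.0% |
| 0.25 | 0.036 | 5.2% |
| 0.5 | 0.071 | 6.0% |
| 1.0 | 0.143 | 8.9% |

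For scale, the article quotes a minimum clinically important difference of 1.6 to 1.9 points.

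The form of the bias matters. The table takes the bias as a shift between the two levels of one factor. Suppose instead that the rater favoured any client with an added component, equally, by b points. Three of the four cells would then shift. The listening main effect would be biased by b − (b + 0)/2 = b/2, and the breathing effect by the same amount. A 1-point shift would then give 0.5 points and about 6.0%.

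**The case against.** The strongest reply is that nothing shows the blind to be broken. The feedback is general and does not ask about components or allocation. The reminder applies at this same visit. If the assessor scores first, the primary rating is untouched. What remains exposed is then the 6-month MADRS and GAF, which are secondary and declared exploratory. The order of tasks is also a detail that an article may leave to the full protocol.

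Most of this stands, and it limits the point. A reader might infer that the feedback question defeats the blinding, or that the primary result is biased. The documents support neither. They show a risk that depends on what clients say and, for the primary outcome, on an order that is not stated.

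Two further inferences also lack support:

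- **Data entry.** The article says that "Data entries are always made by an assessor who is very familiar with the assessment instruments", and one might think that forms revealing the arm pass through that person's hands. But most data are collected electronically, paper is only a contingency, listening is logged by an application on the university server, and access to folders is restricted. No passage shows such forms reaching the assessor.
- **Direction of bias.** One might suppose that the rater shares the investigators' hope that the added components help. The article describes the assessor's qualification and says nothing about expectations.

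The reply does not remove the conflict itself. This is a stated procedure that works against a stated safeguard, so it is more than an omitted detail.

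**Conclusion.** The point holds as a conflict to be reconciled. The blinding statement and the feedback task assign incompatible duties to one person, and the assessor's blind is put at avoidable risk. The 6-week MADRS and GAF are exposed only if feedback precedes scoring. The 6-month MADRS and GAF are exposed under either order, on the assumption that the same assessor rates them, which the Assessment section implies but does not state outright. HADS-A and RAND-36 do not depend on the rater's blind.

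Neither the size nor the direction of any bias can be taken from the documents. The 5.2% to 9% range for the error rate rests on an assumed 0.25 to 1 point of differential bias, SD 7 and a simple 34 v 34 comparison in place of the planned mixed model. The 9% is the worst corner of those assumptions and should not be quoted alone.

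**What to change.** - Reconcile Randomisation and sample size with Safety assessments by taking the feedback question from the assessor. Collect it through the electronic questionnaire already in use after sessions, and withhold the answers from the assessor until after the 6-month rating. The study coordinator is not a suitable substitute, because that role has access to the allocation list.
- If the assessor must keep the question, score and lock MADRS and GAF before any feedback is asked. This protects the 6-week rating only. The 6-month rating would then need a rater who has not heard the feedback.
- Have the assessor record at each visit whether allocation was revealed, and report the counts by arm.
- Treat any analysis that drops unblinded ratings as supportive only. The exclusion happens after randomisation and may differ by arm, since clients with music therapy alone have no added component to mention.
- For visits already completed, report the order that was used and any known unblinding. Trial status says that the target number of therapy processes was reached by the end of March 2019 and that assessments run to the end of 2019. Moving the question may therefore help few 6-week visits, and most of what can still be protected is at follow-up.

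The cost is one question moved to an existing channel, one extra item on the assessment form and a short statement in the report. A second rater at 6 months, if chosen, would need some extra staff time.

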### Statistical analyses and data management

The statistical analyses will follow an intention-to-treat approach, using all available data regardless of whether the treatment was received as intended. Furthermore, in the event of missing outcome data, participants will remain in the analysis if at least one follow-up time point is available. Sensitivity analysis will be conducted with multiple imputation for missing data and as a per-protocol analysis (treatment as received). All outcome measures (MADRS, HADS, RAND-36, GAF, one-item rating of current depression severity) provide continuous data and will be examined for normality before statistical tests are conducted. The main effects of each intervention (LH vs no LH; RFB vs no RFB) and their interaction (LH × RFB) will be tested for all outcome measures, using a repeated-measures linear mixed-effects model with LH and RFB as factors. This analysis strategy has the advantage of making full use of the factorial design, such that all 68 participants are available for each comparison (as presented in Table 1). All tests will use two-sided 5% significance level, with no adjustments for multiplicity; secondary outcomes will therefore be regarded as exploratory. No interim analyses of effects will be conducted.

Most of the data obtained through scales, questionnaires, and forms will be collected electronically. Should the data be obtained through paper forms, they will be immediately converted to electronic data. Data entries are always made by an assessor who is very familiar with the assessment instruments and can thus easily recognise inaccurate data. The assessor will also double-check the data entries. All of the collected data will be stored on secure servers from the University of Jyväskylä, which includes daily backups. Dedicated password-protected folders will be used for different types of data, with access rights granted only to those researchers allowed to handle the given data.

Personal records of the participants, such as names, contact details, and consent forms, are stored in a locked room, with access only by the PI, assessor, and study coordinator. In all other contexts, client codes will be used instead of personal information.

The final dataset will only include pseudonymised data, and will be accessible to all of the researchers involved in the project. We are currently not allowed to make any data available to outsiders through a data repository. We might consider amending our ethical permission in the future so as to share part of the data.

We are planning to publish one main study with the primary and secondary outcomes in a psychiatric journal, as well as several articles focusing on specific sub-questions related to the internal mechanisms of IIMT.

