As regards our additional components, a meta-analysis of the effect of HRVB training on stress and anxiety [44] reported large effect sizes with both the pre–post within-group effect size and the between-group analysis comparing HRVB to a control condition yielding Hedges’ *g* of around 0.8. A meta-analysis of the effects of homework assignments on treatment outcome in cognitive and behavioural therapies [45] reported a pooled ES of *d* = 0.48 favouring homework.

With the target sample size already reported (34 in each main effect), a two-sided *t* test at the 5% significance level will have 50% power to detect an effect size of 0.48 (LH) and a 90% power to detect an effect size of 0.8 (RFB). We provide these numbers with reservations and for information only, since these meta-analyses about homework and HRVB were not conducted in an identical setting to our trial. First of all, HRVB was studied as a stand-alone intervention, whereas we are using it in combination with another method. Second, the type of homework used in IIMT (listening back to self-created music improvisations) is arguably quite different from the homework usually given in cognitive behavioural therapies (e.g. exposure, thought diaries, or practice of social skills). Therefore, we acknowledge that the main effects of RFB and LH may be different from those found in the literature. Consequently, our study remains exploratory, and will only provide evidence for possible strong effects of the added components.

The minimum clinically important difference (MCID) for the Montgomery–Åsberg Depression Rating Scale (MADRS) has been reported to vary between 1.6 and 1.9-point changes from baseline when using a distribution-based method [46]. For anchor-based methods, prior studies report a remission cut-off point as a total score of < 9 points after treatment, or that a score of ≤ 5 equals complete or symptom-free remission and ≤ 11 equals remission, and that a decrease in 39% from baseline corresponds to “much improved” on the Clinical Global Impressions Scale. A mean difference of 1.6–1.9 points, with a common SD of around 7 [2], corresponds to an effect size of around 0.25, which is much lower than the effect size for which this study is powered. Thus, the study will not be able to reliably detect an MCID, but will be powered to detect an effect size similar to those found in previous related studies, as described earlier.

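### The primary model states no baseline MADRS adjustment; at an assumed correlation of 0.3 to 0.6, stating it would lift LH power from about 50% to about 53–68%

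*Protocol article*

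**What the plan says.** **Model.** The section Statistical analyses and data management tests the two main effects and LH × RFB for all outcome measures, "using a repeated-measures linear mixed-effects model with LH and RFB as factors". It names no baseline covariate. It does not say whether baseline is one of the repeated outcomes or, if it is, whether the groups share a baseline mean. On error rates it states: "All tests will use two-sided 5% significance level, with no adjustments for multiplicity".

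**Baseline data.** The section Primary outcome says: "At the beginning of the study, MADRS will be administered as part of the screening process". The section Assessment lists three measurement points (baseline, 6 weeks, 6 months) and makes 6 weeks the time point of primary interest. HADS-A, RAND-36 and GAF are collected at the same three points.

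**Power.** In Randomisation and sample size, the calculation is a two-sided 5% t test: "With the target sample size already reported (34 in each main effect"), with "50% power to detect an effect size of 0.48 (LH") and "a 90% power to detect an effect size of 0.8 (RFB"). The article offers these figures with reservations, calls the study exploratory, and says it cannot reliably detect the MCID. For the MCID comparison it works "with a common SD of around 7".

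**Allocation.** Randomisation uses blocks of 4 and 8. No stratification by baseline severity is described.

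**The concern.** Power is the trial's acknowledged weak point: even odds of detecting the LH effect it cites. A baseline MADRS measured on everyone is the cheapest remedy, yet the stated primary model does not use it explicitly. Two readings of the sentence forgo the gain:

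- baseline is left out, so the 6-week contrast is unadjusted;
- baseline is a repeated outcome with freely estimated group means, so the treatment effect is a difference in change from baseline.

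What is at stake is the precision of both main effects. There is also an unspecified choice between adjusted and unadjusted results, which would be better settled before the data are analysed.

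**Working it through.** **Inputs from the article:** 34 v 34 for each main effect (68 in total); two-sided 5%; d = 0.48 (LH) and 0.8 (RFB); SD about 7.

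**Assumptions:** rho, the baseline to 6-week MADRS correlation, is not given and is varied from 0.2 to 0.7. SDs are taken as equal at the two times, and all 68 clients as having 6-week data.

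**Step 1. Reproduce the stated power.** Noncentrality = d × √(34/2), df 66.

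- LH: 0.48 × 4.123 = 1.979, power 49.6% (stated 50%).
- RFB: 0.8 × 4.123 = 3.298, power 90.2% (stated 90%).

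Both agree, so the stated figures take no credit for baseline.

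**Step 2. Relative variance of the three contrasts.**

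- Unadjusted 6-week difference: 1
- Change from baseline: 2(1 − rho)
- Baseline-adjusted: 1 − rho² = (1 − rho)(1 + rho)

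For 0 < rho < 1, 1 − rho² is below 1. It is also below 2(1 − rho), because 1 + rho < 2. Adjustment is therefore more precise than either alternative.

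**Step 3. Power.** The effective effect size is d/√(1 − rho²) when adjusted (df 68 − 5 = 63) and d/√(2(1 − rho)) for change (df 68 − 4 = 64). At rho 0.5, for example, 0.48/√0.75 = 0.554 adjusted and 0.48/√1 = 0.48 for change.

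| Assumed rho | LH unadjusted | LH change score | LH adjusted | Gain over unadjusted (points) | RFB adjusted |
|---|---|---|---|---|---|
| 0.2 | 49.6% | 33.8% | 51.2% | 1.5 | 91.2% |
| 0.3 | 49.6% | 37.8% | 53.3% | 3.7 | 92.6% |
| 0.4 | 49.6% | 42.8% | 56.6% | 7.0 | 94.3% |
| 0.5 | 49.6% | 49.6% | 61.4% | 11.8 | 96.3% |
| 0.6 | 49.6% | 58.7% | 68.3% | 18.7 | 98.2% |
| 0.7 | 49.6% | 71.1% | 77.9% | 28.3 | 99.5% |

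Gains are taken before rounding. Against the change score, the LH gain runs from 17.4 points at rho 0.2 to 6.8 at rho 0.7.

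**Step 4. Interval width.** The SE of the unadjusted difference is 2 × 7/√68 = 1.70 points. The 95% half-width is 2.00 × 1.70 = 3.4 points. At rho 0.5 it is 3.4 × √0.75 = 2.9 points.

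**Step 5. The reading with no material loss.** If baseline is a repeated row with one mean common to the four groups, precision is about that of the covariate model.

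**The case against.** **Silence is not exclusion.** A reader might infer that LH and RFB are the model's only terms, so that baseline is ruled out. The text does not support that. The same sentence tests LH × RFB, and a repeated-measures model implies time and a covariance structure that are not spelled out either. A continuous baseline score would not be called a factor. Baseline is listed among the measurement points, so it may already be a repeated row. This part stands: the article leaves baseline unstated and does not reject it.

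**An article may leave covariates to the analysis plan.** This is a fair limit on the point. However, the article does commit to a primary model, its factors, its interaction and its missing-data rule. Baseline handling belongs with those, because it decides which contrast is estimated and how precisely. If an unseen plan already adjusts, one sentence makes the article agree with it.

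**The loss is not a fixed 12 points.** A reader might take the rho 0.5 figure as the cost. It holds only at that assumed correlation. MADRS also determined eligibility, which may restrict the baseline range and lower rho, and at rho 0.2 the gain is 1.5 points. In addition, the stated 50% describes a t test, not the planned mixed model, so it is a benchmark only.

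**Chance imbalance.** A reader might argue that a baseline difference passes in full into the 6-week contrast. With equal SDs the expected carry-over is rho times the difference, and the unadjusted standard error already allows for it. It is the same precision point and not a bias. Unstratified blocking is not an error.

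**Conclusion.** The point holds in a conditional form. The stated primary model does not say how baseline MADRS is used. Unless it is a covariate or a common-mean repeated row, the analysis is less precise than it could be at no cost in data.

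Under an assumed rho of 0.3 to 0.6, explicit adjustment takes LH power from about 50% to about 53–68% and RFB power from 90% to about 93–98%. At the low end of plausible correlations the LH gain over an unadjusted contrast is negligible; at rho 0.7 it is large. These figures rest on the article's effect sizes and SD, equal SDs over time, complete 6-week data and a correlation that the article does not report. This is a worthwhile improvement and not a flaw that invalidates the analysis. The trial would still be short of conventional power for LH over most of the range.

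**What to change.** In Statistical analyses and data management, state that the primary model takes 6-week and 6-month MADRS as outcomes with baseline MADRS as a covariate, and that the 6-week LH and RFB contrasts are primary. An equivalent choice is to keep baseline as a repeated row with a single mean for all four groups. Apply the same rule to HADS-A, RAND-36 and GAF, each with its own baseline.

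Cost: one sentence and about one degree of freedom, with no new data and no additional clients. If the full analysis plan already does this, the sentence only needs to say so.
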